### Data analysis

***Phases 1 and 2.*** For the analysis of quantitative data, descriptive statistics will be used, including measures of frequency, central tendency and dispersion according to the type of variable (quantitative or qualitative). Normality will be calculated with Shapiro-Wilk’s test and homogeneity with Levene’s test. To compare proportions of categorical variables, the chi-square test for contingency tables will be used. In the case of 2 × 2 tables, such tests with Yates correction will be used, and if the expected frequency is ≤ 5, Fisher’s exact test will be used. To compare mean values between the quantitative variables of two groups, Student’s t test for independent samples will be used. For the comparison of the mean values between quantitative variables and hospitals, the one-factor ANOVA test and ad-hoc tests with correction by GT2 Hochberg (if variance is homogeneous) or Games Howell (if variance is unequal) will be used. For the correlation between the quantitative variables, Pearson’s correlation coefficient will be used. For the logistic regression, multivariate analysis will be used.

All hypothesis tests will be bilateral. All tests with a confidence level of 95 % (p < 0.05) will be considered statistically significant.

Simple and multi-component Cosinor analyses will be used to explore temporal patterns [34]. This analysis uses the least squares method to approximate the time series of data to obtain one or more harmonics that fit the wavy shape that best explain the variance of the data set. The proportion of the overall variance (PR) represented by each harmonic component and the final multi-component curve function serve as goodness of fit parameters; the higher the PR is, the better representation by the total variance of the harmonic. The F-test statistic applied to the variance, represented by an approximation of the cosine curve versus a linear approximation of the time series data, was used to reject the null hypothesis of zero amplitude (absence of cyclical variation with respect to the period of time explored). The statistical significance of temporal patterns will be verified when the null hypothesis rejected for the F-test statistic is p < 0.5. The descriptive parameters of the statistically significant temporal patterns are the statistical estimated mean rhythm line (MESOR, the estimated rhythmic mean of the time series), amplitude (A, the numerical difference between the peak and valley values), temporal peak (φ, orthophase) and temporal valley (bathyphase); these last two variables are expressed according to the local midnight (00:00 h). The prominence of the temporal patterns, in terms of amplitude, will be expressed according to the MESOR as % AMP (greater prominence of the temporal variation, if the % AMP is greater). The variation will be low if % AMP < 25, moderate if 26–50, and high if > 50. To carry out the simple and multi-component Cosinor analyses, Chronolab software will be used [34].

***Phase 3.*** Analysis of the content of the focus groups will be carry out as follow: (i) transcription content; (ii) data reduction; (iii) exposure of the data; and (iv) conclusions and verification. The analysis of transcription content is approached from two perspectives—Analysis of the narrative (how is it counted?) and thematic/categorical analysis (what is counted?). In the data reduction phase, the facilitating method is the Giorgi Method (1997). The following steps are identified in it: reading the documents to obtain a global meaning; second reading to select the “units of meaning”, or fragments of the text that reveal something important regarding the object of the study; interpretation of meaning units to group them into “meaning statements”; statements of meaning are grouped into “common themes”; the relationship between meaning statements and common themes with the starting categories of the study;, and showing the emerging categories. This analysis will be complemented with the study of the annotations collected in the field notebook during the group interview. To conclude the analysis, a triangulation process will be carried out for researchers, study subjects and data collection techniques.

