## Background

The proportion of older people in the general population has increased during the last few years. Consequently, an important challenge of the public health system is to preserve the autonomy and independence of this group. One of the greatest causes of loss of autonomy and independence are accidental falls and related injuries. Epidemiology shows that accidental falls are not only a main and common problem among older people all around the world but also a big issue in terms of social and economic repercussions for the victims and their families. [1]

Hospital falls imply a greater challenge for healthcare organizations due to their effect on the patient’s quality of life (due partly to the loss of autonomy and independence). In addition, they increase morbidity and length of stay in hospitals, leading to an important rise of the sanitary outlay [2, 3].

Falls in older people are due to intrinsic and extrinsic factors [4]. Even though many studies have been conducted to identify the causality of falls, the time of falls is often not considered [5]. Evidence suggests temporal patterns in the occurrence of hospital falls [6]. Research in temporal patterns in the manifestation and intensity of symptoms and risk of life-threatening and life-ending events (chronopathology and chronorisk) is essential to develop longitudinal (chrono)preventive and (chrono)therapeutic interventions and strategies that take into account the aforementioned patterns [7, 8]. Therefore, this study aims to implement longitudinal preventive counter-measures based on temporal patterns of incident events and relative risk factors for falls and related injuries (*chronoprevention*).

The risk of fall is directly correlated to ageing, so the number of accidental falls will proportionally grow with the ageing of general population [4, 9]. Recent studies show that 30 % of people living among their communities suffer one fall per year [10], rising to 40 % among hospitalized people [11]. Regarding hospitalized people, fall rates show a great variability, between 2 and 17 falls per 1,000 occupied beds [12, 13].

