### Inclusion and exclusion criteria

***Phase 1.*** Regarding patients, they should have been admitted in the aforementioned hospitals, should be over 65 years old and suffer an in-hospital fall. Furthermore, they should sign an informed consent accepting to participate in the study.

Healthcare professionals should have the following requirements: to sign an informed consent accepting to take part in the study and to be nurses in charge of the care of older people suffering from hospital falls, despite not witnessing the event.

Patients who suffer from hospital falls and healthcare professionals who take care of them will be included in the study continuously, which means after every single fall event.

In both cases (patients and healthcare professionals), the sampling will be total.

***Phase 2.*** Records of falls suffered in patients over 65 years old collected in different institutional databases (adverse event report, clinical record of the patient…) in the four hospitals. As in phase 1, the sampling will be total.

***Phase 3.*** Selection of healthcare professionals will be intentional and with the leverage of the collaboration with the centres involved. One person for each sector (doctors, nurses and nursing assistants). Inclusion criteria will be: (i) healthcare professional who has worked in the four hospitals during the time the longitudinal study is carried on; (ii) professionals of clinical units where hospital falls will be recorded during the longitudinal study; and (iii) professionals of clinical units in that are important to the risk of in-hospital falls, by pathologies, dependence, motor or mobility disorder, etc.

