### Study variables

The main dependent variable will be the number of hospital falls. A hospital fall will be defined as “the consequence of a non-intentional and sudden movement towards the floor from a more elevated position” in hospital settings.

Other independent variables related with the patient who experiences a hospital fall include: (i) sociodemographic and economic data (age, gender, marital status and level of education); (ii) time (hour and minute, day and shift work) of fall; (iii) patient position (from the bed with or without bedrails, sitting, walking, and so on) and witness of the fall (roommate, family member, healthcare professional or no witness); (iv) use/no use of footwear and kind (open or closed); (v) cause of fall (instability (general instability and balance loss), dizziness (syncope, fainting and cardiovascular accident), drug adverse effects (diuretics, anti-hypertension and other drugs), accident (event with no identifiable cause), ambient-related (dropped objects, obstacles and wet floor), fragility (extreme fragility or weakness) or others); (vi) location of the fall (hospital room, bathroom, corridor, public area or others); (vii) fall-related injuries and severity (no wound/no consequences, minor wounds (grazes and minor contusions), afflicting wounds (contusions requiring stitches, fractures and skull trauma) or others (not afflicting wounds but still in need of minor medical intervention)); (viii) number and kind of coexisting clinical conditions; (ix) prescribed drugs and their time of administration; (x) chronotype measured by the Horne-Östberg Questionnaire (1976); (xi) quality of life in terms of body functionality, physical limitations, body pain, social role or function, mental health, emotional limitations, vitality, energy or fatigue and general perception about own health; and (xii) general health status in terms of somatic symptoms, anxiety, insomnia, social dysfunction and depressive symptoms.

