After obtaining and analysing the falls that occurred during the first 18 months of the study, time-adjusted preventive measures will be carried out. These measures will be focused on organizational, educational and behavioural elements (previously mentioned).

The establishment of the programme of time-adjusted prevention measures will be carried out in May 2019 in the four centres. The post-intervention data collection will cover July 2019 to September 2020. The managers responsible for each centre, together with the research team, will implement the measures, and, as in the first phase, seminars will be held with healthcare professionals to focus on the recording of falls and their circumstances, as well as the variables included in the prevention programme.

During the post-intervention phase, the individual monthly audits will continue to be carried out with each Clinical Management Unit. This follow-up will make it possible to discern the effectiveness of the preventive measures.

***Phase 2***: For the retrospective study, the data will be delivered by the centres participating in the project to the Principal Investigator anonymized.

***Phase 3***: The development of the focus groups will be carried out in the facilities of the participating hospitals, ensuring the confidentiality of the participants. Four focus groups will be held at the Reina Sofia University Hospital in Córdoba and one in each of the three regional centres.

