The findings that are expected to be found will be transferable to the institution and, in addition, the expected decrease in the incidence of falls will mean a reduction in healthcare costs. The findings endorsed by previous studies carried out in Italian hospitals [20, 39] showed interesting results.

The hourly categorization of fall events according to the evaluated intrinsic and extrinsic risk factors allows for a more precise understanding of their epidemiology and, ultimately, the improvement of the instituted prevention programme. Therefore, the results are likely to generate clinical practice guidelines [6, 24].

The results of this project are intended to promote a more exhaustive investigation of falls, thereby improving initiatives for their prevention. Furthermore, the study interventions emphasize the importance of recording in-hospital falls and their circumstances, especially time. The proposed registration system could be easily implemented and represents a change in health policy. The application of preventive measures according to time (*chronoprevention)* applied in this study will influence the reduction in the number of hospital falls considerably.

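### The main outcome is a raw number of falls, and neither the listed variables nor the listed tests bring in patient activity, so a change in activity can pass for, or hide, a programme effect

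*Protocol article*

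**What the plan says.** All references are to the protocol article.

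- **Outcome.** Study variables: "The main dependent variable will be the number of hospital falls". The lists that follow cover the fall, the patient and the nurse in detail. None of the items is admissions, bed-days or occupied beds.
- **Sample.** Inclusion and exclusion criteria: patients "should be over 65 years old and suffer an in-hospital fall". Phase 2 likewise collects fall records only.
- **Periods.** Design gives a first step of 18 months and a second of 15. Data collection: Procedure agrees on the second: "The post-intervention data collection will cover July 2019 to September 2020". The Phase 2 paragraph of Design dates the phases January 2018 to May 2019 and June 2019 to September 2020, which is 17 and 16 months.
- **Tests.** Data analysis lists chi-square and Fisher tests; a t test, introduced with "To compare mean values between the quantitative variables of two groups"; "For the comparison of the mean values between quantitative variables and hospitals, the one-factor ANOVA test"; Pearson correlation; and a logistic regression with no named outcome. The Cosinor F-test "was used to reject the null hypothesis of zero amplitude".
- **Rate language elsewhere.** Background: "fall rates show a great variability, between 2 and 17 falls per 1,000 occupied beds". Discussion: "the expected decrease in the incidence of falls will mean a reduction in healthcare costs".

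**The concern.** The main aim is the effect of the programme, and the Discussion expects a lower incidence. Incidence needs a denominator. The number of falls can go down because the second period is shorter or because fewer older patients were in hospital, with no change in anyone's risk. It can also stay level while risk drops, if the wards were busier. There is no concurrent control group to absorb such a change. Because every included patient has fallen, the contingency tables and the logistic regression can describe the falls but cannot estimate the risk of falling. Followed as written, the analysis could credit the programme with a change in bed occupancy, or miss a real benefit.

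**Working it through.** The plan states no sample size, expected number of falls or activity figure, so there is no figure of its own to reproduce.

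**1. Listed methods against the main comparison**

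| Method | What it can do here | Exposure term |
|---|---|---|
| Chi-square, Fisher, logistic regression | Describe features of falls among fallers | None |
| t test, two unnamed groups | Could compare mean monthly counts before and after, but is not assigned to this | None |
| One-factor ANOVA | Compares hospitals with each other; with one factor it cannot also hold period | None |
| Pearson correlation | Association between quantitative variables | None |
| Cosinor F-test | Tests zero amplitude, not a change in level | None |

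**2. Period length, if totals were compared**

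Input: the months in the article. Expected post/pre ratio with no effect and constant activity = post months / pre months.

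- 15/18 = 0.833, a drop of 16.7%.
- 16/17 = 0.941, a drop of 5.9%.

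**3. Activity, under the most favourable reading (t test on 18 v 15 monthly totals)**

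Assumptions, because the article gives no volumes: M = 10, 20 or 40 falls a month over the four hospitals before the programme; bed-days multiplied by c afterwards; true rate ratio R; variance φ times the mean. The expected t statistic is about

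d = M(1 − cR) / √[φ(M/18 + McR/15)],

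and the chance of a significant decrease is about P(Z > 2.04 − d), where 2.04 is the 5% two-sided critical value on 31 degrees of freedom.

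*False decrease* (c = 0.90, R = 1, φ = 1):

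- M = 10: d = 1/√(0.556 + 0.600) = 0.93, giving 13%.
- M = 20: d = 2/√(1.111 + 1.200) = 1.32, giving 24%.
- M = 40: d = 4/√(2.222 + 2.400) = 1.86, giving 43%.

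Simulation (20,000 runs or more) gives 14 to 15%, 25% and 43%. With c = 0.95 it gives about 7%, 10% and 14%. With φ = 2, d is divided by √2 and the results at c = 0.90 are about 9%, 14% and 24%. The nominal figure for a decrease is 2.5%.

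*Hidden benefit* (c = 1.10, R = 0.80, so cR = 0.88, φ = 1):

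- t test: d = 1.2/√(0.556 + 0.587) = 1.12 at M = 10. Simulated power is 19%, 33% and 59% at M = 10, 20 and 40.
- Model with a bed-days offset: |ln 0.80| / √(1/180 + 1/132) = 0.223/0.1146 = 1.95 at M = 10. Power is 50%, 79% and 98%.

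*Equal activity* (c = 1, R = 0.80, M = 20): 74% for the t test and 77% for the model. The gain is therefore the activity adjustment, not power as such.

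**4. The model must allow for overdispersion**

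With no effect and Poisson variance, the offset model rejects in 5% of runs two-sided, which is about 2.4% as a decrease. At twice-Poisson variance a plain Poisson offset model rejects in about 17% two-sided. A quasi-Poisson version holds 5%.

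**The case against.** The strongest reply is that this is a condensed article. The main model, the denominator and the unit of analysis are often left to a fuller plan, which is not shown and may name a rate. The Data analysis section is a generic list, and the text speaks of incidence several times, so a rate may well be intended. This stands to the extent that an unassigned test alone would not be a finding. It does not dispose of the point, because the article does fix things: a count as the outcome, fallers only as the sample, a detailed variable list with no denominator, and tests named down to their post-hoc corrections. A denominator is also a matter of data collection, not only of analysis.

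Three stronger readings are tempting, and the documents do not support them:

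- **That totals over 18 and 15 months will be compared.** Nothing says so. The 16.7% and 5.9% apply only if that is done, and monthly counts avoid them.
- **That hospital is ignored.** It is the factor in the ANOVA, and secondary aim (ii) looks at hospital setting before and after the intervention. The ANOVA simply does not address change within a hospital.
- **That level is ignored by the Cosinor analysis.** The MESOR is a level parameter, and patterns are to be obtained before and after. But no pre/post test of the MESOR is named, and it too would rest on counts without exposure.

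It is also fair that volumes and activity changes are assumed, and that overdispersion shrinks the false-decrease figures. They remain several times the nominal 2.5%.

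**Conclusion.** The point holds in this form: a raw count among fallers, over unequal periods, with no activity denominator in the listed variables or tests, cannot separate the programme from a change in patient activity. The period-length effect (16.7% or 5.9%) follows from the article's own dates but is conditional on comparing totals. The activity effect is illustrative. With 10% fewer bed-days and unchanged risk, a false significant decrease arises in about 15%, 25% and 43% of runs under Poisson variance and 9%, 14% and 24% at twice that variance, for assumed volumes of 10, 20 and 40 falls a month. If activity did not change, the t test on monthly totals would do nearly as well as the rate model. The article does not show that activity changed, and a reader should not infer that the result will be biased in a known direction. The change is worth making because it is cheap and matches the incidence claim that the article makes. The unseen full plan may already contain it.

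**What to change.** In Study variables, define the main outcome as falls per 1,000 bed-days of patients over 65, and add monthly bed-days per hospital to the data collected.

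In Data analysis, name the main analysis: monthly falls per hospital in a negative binomial or quasi-Poisson model (not plain Poisson), with period and hospital terms and a log bed-days offset. Report the pre/post rate ratio with its 95% CI. Since Limitations says the intervention is adapted to each centre, describe the ratio as the average effect of a locally tailored programme. Present hospital-specific ratios descriptively.

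**Cost.** Bed-days must be obtained from hospital records; patients and nurses carry no extra burden.

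**Precision to expect.** With an assumed rate ratio of 0.70, the interval is 0.70 × exp(±1.96√[φ(1/pre + 1/post)]), where pre = 18M and post = 15M × 0.70.

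- Combined, φ = 1, M = 10, 20, 40: 0.55–0.89, 0.59–0.83, 0.62–0.79.
- Combined, φ = 2: 0.50–0.98, 0.55–0.89, 0.59–0.83.
- One hospital, φ = 1, with 1 or 6 falls a month: 0.33–1.50 or 0.51–0.96. This is why hospital-specific results should stay descriptive.

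**Limit.** The model adjusts for activity and hospital mix. It does not remove secular trends or changes in how completely falls are recorded, and the report should say so.

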### Participants and setting

***Phase 1.*** The study subjects will be all those patients over 65 years of age who suffer one/several fall(s) during their admission to the Reina Sofia University Hospital in Córdoba and in the three regional hospitals of the Province of Córdoba (Cabra, Montilla and Pozoblanco) from January 2018 to September 2020.

Specifically, for the study of the levels of fatigue/sleepiness, attention and cognitive functionality of the healthcare professionals, the reference nurses of the older person who has an in-hospital fall during the study period will also be included.

***Phase 2.*** Institutional records of falls occurring in patients over 65 years old. In order to contrast with the prospective design, the institutional records of the four hospitals will be collected during the same period (January 2018 to September 2020).

***Phase 3.*** Healthcare professionals (doctors, nurses and nursing assistants) will be interviewed.

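### The plan handles unequal variances only in the post-hoc hospital comparisons; the overall ANOVA F and Student's t have no unequal-variance version (secondary variables, low severity)

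*Protocol article*

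**What the plan says.** All of this stands in the Data analysis section of the protocol article, under Phases 1 and 2.

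- Variances are to be checked: "homogeneity with Levene’s test".
- Two groups: "To compare mean values between the quantitative variables of two groups, Student’s t test for independent samples will be used". No unequal-variance version is named, and none is excluded.
- Across hospitals: "the one-factor ANOVA test and ad-hoc tests with correction by GT2 Hochberg (if variance is homogeneous) or Games Howell (if variance is unequal"). The condition on variance is attached to the follow-up tests. None is attached to the overall test.
- Error level: "All hypothesis tests will be bilateral", and "All tests with a confidence level of 95 % (p < 0.05) will be considered statistically significant".

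Participants and setting names "the Reina Sofia University Hospital in Córdoba and in the three regional hospitals of the Province of Córdoba". Inclusion and exclusion criteria says that all eligible falls are taken, so group sizes follow the volume of each hospital. The article gives no number of falls, patients or nurses per hospital, and no SD.

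**The concern.** The classical one-factor F test compares the spread of the group means with a single pooled variance. If variances differ and group sizes differ too, that pooled variance is the wrong yardstick. When the smaller groups have the larger spread, the test rejects too often. When the larger group has the larger spread, it rejects too rarely.

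The plan foresees unequal variances, since it names Games-Howell for that case, but it leaves the preceding step unchanged. Unequal group sizes are a fair expectation with one university hospital and three regional ones and no sampling quota. The Procedure section also plans four focus groups at the university hospital and one at each regional centre.

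At stake is the overall p-value for differences between hospitals in quantitative measures such as age, quality of life, sleep quality and sleepiness. It could be reported against 5% when its real error rate is well above or well below that.

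**Working it through.** **Inputs.** From the article: two-sided 5%, four hospitals (one university, three regional), and steps of 18 and 15 months (Design section). Assumed, because not given: hospital sizes from 1:1 to 10:1, and an SD ratio r (small hospitals to large) from 0.5 to 2. The data are normal with equal true means. The 5% level is an input, so the plan has no derived figure to reproduce.

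**Why the F test drifts.** With equal means, group sizes n_i, total N, k = 4 groups and variances σ_i²:

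- E(MS between) = Σ(1 − n_i/N)σ_i² / (k − 1)
- E(MS within) = Σ(n_i − 1)σ_i² / (N − k)

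For 200/50/50/50 with r = 2:

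- between = (0.4286 × 1 + 3 × 0.8571 × 4)/3 = 3.57
- within = (199 + 3 × 49 × 4)/346 = 2.27
- F is centred near 3.57/2.27 = 1.57 instead of 1, so it rejects too often.

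For the same sizes with r = 0.5:

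- between = (0.4286 + 3 × 0.8571 × 0.25)/3 = 0.357
- within = (199 + 3 × 49 × 0.25)/346 = 0.681
- The ratio is 0.52, so it rejects too rarely.

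With equal sizes the two expectations coincide for any r.

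**Simulated rejection rate of the F test** (nominal 5%, 20,000 runs per cell; Monte Carlo standard error at 5% is √(0.05 × 0.95/20,000) = 0.15 percentage points):

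| Sizes | r = 0.5 | 0.67 | 0.8 | 1 | 1.25 | 1.5 | 2 |
|---|---|---|---|---|---|---|---|
| 100/100/100/100 | 6.4% | 5.6% | 5.1% | 4.7% | 4.8% | 5.6% | 5.6% |
| 200/100/100/100 | 2.3% | 2.7% | 3.6% | 4.9% | 6.7% | 8.0% | 9.1% |
| 200/50/50/50 | 0.5% | 1.3% | 2.3% | 5.0% | 8.8% | 12.2% | 17.2% |
| 300/30/30/30 | <0.1% | 0.4% | 1.3% | 5.0% | 12.1% | 20.2% | 31.9% |

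Welch's ANOVA gave 4.8% to 5.3% in every cell. A repeat with 200,000 runs per cell agreed with the F-test figures to within 0.5 percentage points.

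**Does Levene's test protect the overall test?** At 200/50/50/50 with r = 1.5, Levene's test rejected in 99% of 3,000 runs. Among those runs the F test rejected in 12.8%. As written, the plan would detect the problem and still report the same F test.

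**Two groups, before against after.** At a constant monthly number of falls, 18 and 15 months give a ratio of 1.2, for example 180 against 150. In large samples the size of the pooled t test is 2Φ(−1.96 × √(V_pooled/V_true)), where V is the variance of the difference in means.

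- Second-period SD doubled: V_pooled = [(179 + 149 × 4)/328] × (1/180 + 1/150) = 0.02888. V_true = 1/180 + 4/150 = 0.03222. Size = 2Φ(−1.856) = 6.4%.
- Second-period SD halved: V_pooled = [(179 + 149 × 0.25)/328] × (1/180 + 1/150) = 0.00806. V_true = 1/180 + 0.25/150 = 0.00722. Size = 2Φ(−2.070) = 3.8%.

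If the periods were less balanced, at 150 against 100, simulation gives 2.7% to 7.9% over the same SD ratios. Welch's t stays at 4.8% to 5.3% there.

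**The case against.** Much can be said for the plan.

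- **The sizes are assumed.** A reader might infer that these tests run at two to six times the stated 5%. The article does not support that. It gives neither sizes nor SDs, and nothing in it says that the smaller hospitals have the larger spread. Six times needs roughly 10:1 with an SD ratio of 2, while the reverse pattern gives rates below 5%.
- **Pairwise hospital claims are already covered.** Under unequal variances the plan uses Games-Howell, so a statement that one particular hospital differs from another rests on a suitable test. Only the overall p-value is exposed. The article does not say whether the follow-up is run only after a significant F. If it is, an F test that rejects too rarely could also block it.
- **The t test is a weaker case.** A reader might apply the hospital imbalance to it, but one hospital against another is a post-hoc comparison in this plan. The natural two-group use is before against after, where the effect is small. As a Welch version is not ruled out, the gap there is partly one of wording.
- **Levene's test.** The article nowhere says that a non-significant result would be taken as proof of equal variances.
- **The main outcome is untouched.** Study variables names the number of falls as the main dependent variable, and temporal patterns are analysed by Cosinor.
- **This is a condensed article.** Detail can be left to an analysis plan. But the rule for unequal variances is spelled out down to the named post-hoc procedures, so its stopping short of the overall test is a feature of the rule and not an omission through brevity.

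All but the last of these points stand, and they limit the size of the problem. They do not remove the mismatch between the overall and follow-up tests.

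**Conclusion.** The point holds in a narrow form. The rule for unequal variances covers the post-hoc hospital comparisons and misses the overall F test, and Student's t is named without an unequal-variance version. For the assumed sizes (2:1 to 10:1) and SD ratios (0.5 to 2), the F test's error rate lies anywhere from below 0.1% to about 32%, in either direction from 5% depending on which hospitals have the larger spread. With equal sizes it stays at about 5% to 6.5%. A near-balanced before-after t test stays at about 4% to 6.5%. These are ranges under stated assumptions and do not predict what this trial will show. The consequence is confined to secondary quantitative variables. Severity is low.

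**What to change.** Replace the two sentences on means with one rule:

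- across hospitals, Welch's ANOVA followed by Games-Howell, whatever Levene's test shows;
- for two independent groups, Welch's t test;
- Levene's test reported as description, not used to choose a test.

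This is a one-line change using standard software options. It affects neither the design nor data collection. The cost is a small loss of power when variances are in fact equal. In a check with equal SDs at 200/50/50/50, with the three smaller hospitals 0.4 SD from the large one, power was 88.5% for the F test and 87.8% for Welch's ANOVA. In the least favourable case tried (300/30/30/30, one small hospital 0.6 SD from the rest) it was 75.4% against 72.2%.
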